#### *Blood Samples for Laboratory Tests*

Samples for Laboratory A and B will be analyzed at the central laboratory.

Blood samples for Laboratory A will be drawn on Day 1 and Day 2 prior to infusion with study medication.

The following samples will also be drawn on Days 1 and 2 prior to infusion with study medication:

- A reserve sample (see Section 9.3.1)
- Serum for IgG levels

The following will be drawn on Day 1 only prior to infusion with study medication:

- Laboratory B
- A retention sample (see Section 9.3.1)
- A sample for a Direct Coombs' Test on Day 1 only (see Section 9.3.2)
- NAT for HCV, HIV and Parvovirus B19 on Day 1 only
- Serology for HIV1 and HIV2, HCV, and HBsAg on Day 1 only

#### *Urinalysis*

A urine sample for urinalysis on Day 1 only

#### *Adverse Events*

All AEs reported by the subject, recorded on the diary card or observed by the investigator will be recorded (Section 9.1.1).

#### *Assessment for Bleeding/Hemorrhage*

At each visit, the subject will be assessed for bleeding and hemorrhage; this will be graded as detailed in Appendix 1 and recorded in the subject's CRF (along with any bleeding episodes recorded in the subject's diary card).

*Concomitant medications*

All concomitant medications, including any entries on the diary cards, must be recorded in the subject's CRF including corticosteroids and immunosuppressants, if applicable (see also Section 5.3.1.1).

*Diary Card*

Each subject will be provided with a diary card at the first infusion visit. Subjects will be instructed to complete a diary entry every day from Day 1 until Day 32 describing any AEs and concomitant medications. Subjects should also document in their diaries any bleeding episodes, or the absence of such episodes, every day.

At each visit from Day 1 to Day 32, the study nurse will review the diary cards, and details of AEs, bleeding episodes, and concomitant medications will be entered in the subject's CRF. The study nurse will collect diaries at the Day 32 follow-up visit.

*GAMMAPLEX Infusion*

Each subject will be treated with GAMMAPLEX at a total dose of 2 g/kg body weight divided over 2 consecutive days (i.e., 1 g/kg on Day 1 and 1 g/kg on Day 2). IGIV will be infused by means of an infusion pump for precise infusion rates. (See Section 7.2 for details on treatment, dosing, and administration).

At the discretion of the investigator, if the subject is capable, he/she will be allowed to leave the study center after the completion of the assessment 60 minutes after the infusion.

**5.3.1.3. Follow-Up Visits for First Treatment Course (Days 3, 5, 9, 14, 21 and 32)**

At each visit the following will be done:

*Interval Medical History*

Any changes from the previous medical history on Day 1 should be recorded in the CRF.

*Physical Examination*

A physical examination will be performed at every visit and the results recorded in the CRF.

*Vital Signs*

Vital signs assessed by qualified personnel will be entered in the CRF at the Visits on Days 3, 5, and 9 only.

*Blood Samples for Laboratory Tests*

- Blood samples for Laboratory A will be drawn at each of the follow-up visits (Days 3, 5, 9, 14, 21, and 32).
- Samples for Laboratory B will be drawn on Days 3 and 9 and Day 32.
- Serum for IgG levels will be drawn at each visit
- Samples for Direct Coombs' Test will be taken on Day 5 and Day 14. (see Section 9.3.2). Samples for LDH, haptoglobin, and urine hemosiderin will also be taken on Day 5 and Day 14.

- NAT for Parvovirus B19 on Day 9 and Day 32.
- NAT for HCV and HIV on Day 32.
- Serology for HIV1 and HIV2, HCV, HBsAg on Day 32. Any seroconversion should be followed up.
- A reserve sample will be taken at each visit

### *Urinalysis*

A urine sample for urinalysis will be taken on Days 3, 9, and 32.

### *Adverse Events*

All AEs reported by the subject, recorded on the diary cards, or observed by the investigator will be recorded at these visits (see Section 9.1.1). On Day 5, particular attention should be paid to accurately collecting and recording all AEs that occur in the first 72 h after completion of the treatment course (see Section 10.4.1).

### *Assessment for Bleeding/hemorrhage*

See Section 5.3.1.2.

### *Concomitant medications*

Concomitant medications will be recorded at these visits, including entries on the diary cards. See Sections 5.3.1.1 and 5.3.1.2.

### *Diary Card:*

At each visit, diary cards will be reviewed, and details of AEs, bleeding episodes, and concomitant medications will be entered on the CRF. See above and Section 5.3.1.2.

#### **5.3.1.4. Infusion Visits for Additional Treatment Course(s) (Infusions 3–6)**

Additional treatment courses are not mandatory, but they can be considered if the platelet count drops below  $25 \times 10^9/L$ . If the study physician/investigator deems it necessary on clinical grounds to give the IGIV during the period 32 to 90 days following the first treatment course, he/she, at his/her discretion, may give another 1 or 2 courses of GAMMAPLEX (treatment courses 2 and 3). See Figure 1 and Table 2.

If, however, it is considered that a second course of GAMMAPLEX would be appropriate after Day 9 and before Day 32, investigators must discuss this with the medical monitor and sponsor before proceeding. The administration of GAMMAPLEX during this period would interfere with the analysis of the duration of effect of GAMMAPLEX, an important secondary efficacy variable.

Before the first infusion of GAMMAPLEX in each additional treatment course, the following will be done (as detailed in Section 5.3.1.2):

*Interval Medical History**Physical Examination**Vital Signs**Blood Samples for Laboratory Tests*

The following samples will be taken before dosing on the first day of the treatment course only

- Platelet count (local laboratory)
- Blood for Laboratory B

Samples for Laboratory A will be collected at each infusion visit.

*Direct Coombs' Test before the first infusion of each treatment course (see Section 9.3.2)*

*Reserve sample before the first infusion of each treatment course. (See Section 9.3.1)*

*Urinalysis before the first infusion of each treatment course*

*GAMMAPLEX Infusion*

Each subject will be treated with GAMMAPLEX at a total dose of 2 g/kg body weight divided over 2 consecutive days, i.e., 1 g/kg on Day X and 1 g/kg on Day X+1 (see Sections 5.3.1.2 and 7.2). The date of additional treatment courses will be decided by the investigator based upon the subject's response to the first treatment course (for the second treatment course) and the second treatment course (for the third treatment course).

*Adverse Events**Concomitant medications***5.3.1.5. Follow-Up Visits for Additional Treatment Course(s) (Infusions 3–6)**

Subjects will return for a follow-up visit 3 days after the end of each of the second and third treatment courses, if they receive them (Day X+4 and Day Y+4 respectively). At those visits, the following will be done (see Section 5.3.1.2 and Table 2):

*Interval Medical History**Physical Examination**Vital Signs**Blood Samples for Laboratory Tests*

The following samples will be taken on Day X+4 and Day Y+4:

- Blood for Laboratory A

- Blood for Laboratory B

*Urinalysis**Direct Coombs' Test*

Samples for LDH, haptoglobin, and urine hemosiderin will also be taken to test for hemolysis (see Section 9.3.2)

*Reserve Sample (see Section 9.3.1)**Adverse Events**Concomitant Medications***5.3.1.6. End of Study Visit**

For all subjects this visit will be approximately 3 months after the first infusion of the last course of GAMMAPLEX and will be the End of Study visit for all subjects irrespective of whether they received 1, 2, or 3 courses. For subjects receiving 1 treatment course of GAMMAPLEX only, this visit will take place on Day 90.

*Interval Medical History*

An interval medical history will be performed. Any changes from the last medical history should be recorded in the CRF. Subjects should not receive any more GAMMAPLEX treatments after this visit.

*Physical Examination*

A final physical examination will be performed at this visit and the results recorded on the CRF.

*Vital Signs*

Vital signs assessed by qualified personnel will be entered in the CRF. **Before listing changes in vital signs as AEs, each change should be assessed for clinical relevance (see Section 9.2).**

*Blood Samples for Laboratory Tests (see Section 9.3.1)*

- Laboratory A
- Laboratory B

*NAT for HCV, HIV, and Parvovirus B19**Serology for HIV1 and HIV2, HCV, and HBsAg**Serum for IgG, IgA, and IgM levels**Reserve Sample**Retention Sample (see Section 9.3.1)*

*Urinalysis*

*Adverse Events*

All AEs reported by the subject or observed by the investigator will be recorded at each visit (see Sections 5.3.1.1 – 5.3.1.4 and 9.1.1).

*Assessment for Bleeding/Hemorrhage*

See Appendix 1.

*Concomitant medications*

See Sections 5.3.1.1 to 5.3.1.4.

**Figure 1 Study Flow Chart**[figure not shown]

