##### *Pregnancy Test*

All female subjects of childbearing potential will receive a urine-based, human chorionic gonadotrophin (HCG) pregnancy test irrespective of claimed inability to conceive.

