##### *Pregnancy Test*

A urine-based HCG test will be done before the infusion with GAMMAPLEX on Day 1.

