**Table 1 Schedule of Assessments**

| Evaluation
(Volume of Blood)       | Visit name/Day/Time relative to first infusion on Day 1 |              |                |              |                  |                   |                    |                     |                     |                     |                     |                        |
|---------------------------------------|---------------------------------------------------------|--------------|----------------|--------------|------------------|-------------------|--------------------|---------------------|---------------------|---------------------|---------------------|------------------------|
|                                       | Screening                                               |              | Infusion 1     | Infusion 2   | Follow-up        | Follow-up         | Follow-up          | Follow-up           | Follow-up           | Follow-up           | Follow-up           | End of Study visit (m) |
|                                       | Full                                                    | Re-check (a) | Day 1          | Day 2        | Day 3
(±12 h) | Day 5
(±1 day) | Day 9
(±2 days) | Day 14
(±2 days) | Day 21
(±2 days) | Day 32
(±2 days) | Day 90
(±7 days) |                        |
| Eligibility                           | X                                                       | X            | X              |              |                  |                   |                    |                     |                     |                     |                     |                        |
| Consent                               | X                                                       |              |                |              |                  |                   |                    |                     |                     |                     |                     |                        |
| HCG Urine Test (fertile females only) | X                                                       |              | X              |              |                  |                   |                    |                     |                     |                     |                     |                        |

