**Table 2 Additional Assessments for Subjects who Require 2 or 3 Courses of GAMMAPLEX (Infusions 3 - 6)**

| Evaluation
(Volume of Blood)    | Visit                 |                         |                                 |                       |                         |                                 |                                                                                                            |
|------------------------------------|-----------------------|-------------------------|---------------------------------|-----------------------|-------------------------|---------------------------------|------------------------------------------------------------------------------------------------------------|
|                                    | Treatment Course 2    |                         |                                 | Treatment Course 3    |                         |                                 | End of Study visit
90 days after the first
infusion of the last course
of GAMMAPLEX
(± 7 days) |
|                                    | Infusion 3
(Day X) | Infusion 4
(Day X+1) | Follow-up
(Day X + 4 ±1 day) | Infusion 5
(Day Y) | Infusion 6
(Day Y+1) | Follow-up
(Day Y + 4 ±1 day) |                                                                                                            |
| Interval Medical History           | X                     | X                       | X                               | X                     | X                       | X                               | X                                                                                                          |
| Physical Examination               | X                     | X                       | X                               | X                     | X                       | X                               | X                                                                                                          |
| Vital Signs (a)                    | X                     | X                       | X                               | X                     | X                       | X                               | X                                                                                                          |

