## 6. STUDY POPULATION

### 6.1. Inclusion Criteria

1. Males and females aged between 18 and 70 years
2. Confirmed diagnosis of chronic ITP of at least 6 months duration.
3. Platelet count  $\leq 20 \times 10^9/L$  at enrollment (local laboratory).
4. Absence of other conditions that, in the opinion of the investigator, could cause thrombocytopenia.
5. If subjects are currently being treated with corticosteroids the treatment regimen/dose must have been stable (for a minimum of 2 weeks before Day 1). However, subjects must remain on a stable treatment regimen. If there is any intent to alter the corticosteroid treatment regimen (e.g., tapering of corticosteroids) before Day 10, subjects may not be included in the study. If possible, doses of corticosteroids or other immunosuppressant medications should remain constant until Day 32. The primary efficacy variable of the study is the platelet count at Day 9. Therefore, changing the subject's medication regimen should be avoided in order to reduce the variables that could have an effect on the platelet count.
6. If subjects are currently being treated with cyclophosphamide, azathioprine or attenuated androgens, the treatment regimen and dose must have been stable for a minimum of 2 months before Day 1. However, if there is any intent to alter the treatment regimen before Day 10, subjects may not be included in the study. If possible, doses of corticosteroids or other immunosuppressant medications should remain constant until Day 32. The primary efficacy variable of the study is the platelet count at Day 9. Therefore, changing the subject's medication regimen should be avoided in order to reduce the variables that could have an effect on the platelet count.
7. Splenectomized subjects and both Rh(D)+ and Rh(D)- subjects can be included.
8. The subject has signed an informed consent form (subjects must be at least 18 years old), and/or the subject's legal guardian has signed the informed consent form if indicated, not more than 6 months prior to Day 1 (see Section 11.3).
9. If a subject is a female of child-bearing potential, she must have a negative result on a urine-based HCG pregnancy test.
10. If a subject is a female who is or becomes sexually active, she must practice contraception by using a method of proven reliability for the duration of the study.

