### **6.3. Subject Withdrawal**

Subjects may be withdrawn from study for any of the following reasons:

1. The subject withdraws from the study on his/her own volition.
2. The subject develops Hepatitis B, Hepatitis C, or HIV as determined by a positive result on a test for HBsAg or on a NAT for HCV or HIV RNA, or the appropriate serological tests for these viruses.
3. The subject has a serious adverse event (SAE) while participating in the study and, at the discretion of the site investigator, is discontinued.
4. The subject becomes pregnant while participating in the study. Any subject that becomes pregnant while participating in the study will not receive any further infusions of GAMMAPLEX.
5. The investigator may withdraw subjects at anytime if they feel it is not in the subject's best interest to continue in the study.

If a subject's Day 1 blood sample results from the central laboratory (for Laboratory A, Laboratory B tests or for the other protocol required blood tests) are out of range, the subject will be withdrawn from the efficacy analysis only. These subjects will still be included in the safety analysis and will therefore continue to attend the follow-up visits. Subjects withdrawn from the efficacy analysis will not be eligible to receive any further courses of GAMMAPLEX.

If a subject receives any of the study product and withdraws, all of the assessments scheduled on Day 32 and the End of Study visit must be done, if possible. For subjects who received more than 1 course of GAMMAPLEX before withdrawal, every effort must be made to complete the assessments scheduled for the End of Study visit.

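### No pregnancy test is scheduled after Day 1, yet courses 2 and 3 may start up to Day 90 and Protocol section 6.3 bars further infusions once a subject is pregnant

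*Protocol*

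**What the plan says.** Pregnancy is an exclusion (section 6.2, item 8). For pregnancies arising on study, section 6.3, item 4, states: "Any subject that becomes pregnant while participating in the study will not receive any further infusions of GAMMAPLEX".

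Testing is specified in two places:

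- **Screening (section 5.3.1.1):** "All female subjects of childbearing potential will receive a urine-based, human chorionic gonadotrophin (HCG) pregnancy test irrespective of claimed inability to conceive".
- **First course (section 5.3.1.2):** "A urine-based HCG test will be done before the infusion with GAMMAPLEX on Day 1".

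The HCG row of Table 1 is marked at those two visits and nowhere else.

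After the first course, a subject may receive one or two more courses, normally between Day 32 and Day 90. Section 5.3.1.4 also allows a second course after Day 9 and before Day 32, following discussion with the medical monitor and sponsor. For these courses the section says "Before the first infusion of GAMMAPLEX in each additional treatment course, the following will be done". It refers back to section 5.3.1.2 and then names the items: interval history, physical examination, vital signs, local platelet count, Laboratory A and B, Direct Coombs' test, reserve sample and urinalysis. A pregnancy test is not among them. Table 2, which schedules Infusions 3 to 6 and the End of Study visit, has no HCG row.

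The standing safeguard is inclusion criterion 10: a woman who is or becomes sexually active must agree that "she must practice contraception by using a method of proven reliability for the duration of the study".

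**The concern.** After course 1, the only infusions left to withhold are Infusions 3 to 6, so the bar in section 6.3, item 4, mainly protects courses 2 and 3. Those are the courses for which the protocol schedules no test. A site following section 5.3.1.4 and Table 2 exactly could re-dose a woman whose pregnancy nobody had recognised, and would have complied with every listed procedure.

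The protocol is stricter at the start of course 1. Contraception, interval history and physical examination all apply on Day 1 as well, and a same-day test is still required in addition to them. Before courses 2 and 3 the test is dropped and only the other safeguards remain.

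What is at stake is subject safety: exposure to the product that the protocol itself forbids. Nothing in the efficacy analysis, sample size or error rate depends on it, because efficacy is assessed on the first course only (section 5.2).

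**Working it through.** The protocol gives no figure on this point to reproduce. The check is a reading of every place where a test could appear, followed by simple date arithmetic.

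**1. Where a pregnancy test is and is not scheduled**

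| Place in the Protocol | HCG test? |
|---|---|
| 5.3.1.1 Screening; Table 1 | Yes |
| 5.3.1.2 Infusion visits, course 1; Table 1 | Yes, Day 1 only |
| 5.3.1.3 Follow-up, Days 3 to 32; Table 1 | No |
| 5.3.1.4 Infusion visits, courses 2 and 3; Table 2 | No |
| 5.3.1.5 Follow-up, courses 2 and 3; Table 2 | No |
| 5.3.1.6 End of Study; Tables 1 and 2 | No |
| 9.3.1 Clinical laboratory tests | No |

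Scheduled tests after Day 1: none. Figure 1 is not reproduced in the text available, but the visit descriptions and both tables agree.

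**2. Could another provision supply the test?**

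- *The cross-reference to section 5.3.1.2.* It introduces a named list that leaves the test out. In section 5.3.1.2 the test is tied to Day 1, whereas additional courses are dated Day X and Day Y.
- *Loose use of Day 1.* Section 9.3.1 and footnote b of Table 2 use Day 1 in connection with later infusions, but in both places only for the local platelet count.
- *Urinalysis.* Section 5.3.1.4 requires "Urinalysis before the first infusion of each treatment course". Table 1 lists urinalysis and HCG as separate rows, so the one does not include the other.

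**3. Age of the last test when an additional course begins** (start day minus Day 1, counting days from Day 1)

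| Start of additional course | Days since last test | Weeks |
|---|---|---|
| Day 10 (earliest by the exception route) | 10 − 1 = 9 | 9 / 7 = 1.3 |
| Day 32 | 32 − 1 = 31 | 31 / 7 = 4.4 |
| Day 90 | 90 − 1 = 89 | 89 / 7 = 12.7 |
| Course 1, for comparison | 0 | 0 |

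For scale, section 5.3.1.2 asks for repeat local safety bloods when screening was more than 14 days before Day 1. Both ends of the normal window exceed that interval.

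**4. Exposure at stake:** 2 courses × 2 infusions × 1 g/kg = 4 g/kg at most.

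**5. Number of tests the fix would add:** the protocol does not say how many women of childbearing potential will be re-treated. At the minimum of 31 evaluable subjects, the ceiling is 31 × 2 = 62 tests, reached only if every subject were such a woman and received both extra courses.

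**The case against.** The case against accepts the reading of the schedule and disputes how much follows from it.

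- **No rule is contradicted.** Section 6.3, item 4, says what to do once pregnancy is known; it does not require surveillance. That is correct. The point is a gap between a prohibition and the procedures that should support it, not two conflicting statements.
- **The Day 1 test has its own purpose.** It confirms eligibility, and screening may be up to six months earlier. Before re-treatment from Day 32, a woman has normally had six follow-up visits with history, examination and adverse-event questioning. This weakens the comparison with course 1 but does not remove it. The Day 1 HCG test is required however recent screening was, while the repeat local safety bloods are waived if screening fell within 14 days. The follow-up visits help only if the pregnancy is noticed.
- **The screening phrase about claimed inability to conceive concerns who is tested.** It does not address whether later self-report of pregnancy is enough. That is fair, and the conclusion here does not rest on that phrase.
- **Follow-up of pregnancies to delivery (section 9.1.1.4) would be only partly helped.** Tests at Day X and Day Y would not cover women who receive one course, or anyone after her last course. This also stands. The argument for the change is the prevention of forbidden dosing, not complete ascertainment of pregnancies.
- **Four infusions is a worst case.** It needs contraception to fail before course 2, both optional courses to be given, and the pregnancy to be missed at each intervening visit. The protocol quantifies no fetal risk. These limits bear on severity; they do not close the gap.

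**Conclusion.** The concern holds. No pregnancy test is scheduled after Day 1. An additional course started in the normal window relies on a test 31 to 89 days old (9 days at the earliest by the exception route), and up to 4 g/kg could be given to a woman with an unrecognised pregnancy, against section 6.3, item 4.

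The intervals assume days counted from Day 1 and the re-treatment window as stated. The 4 g/kg is an upper bound, not an expected exposure; the protocol gives no basis for estimating how many women would be affected. Existing safeguards cover known and suspected pregnancies, so the residual risk is confined to unrecognised ones. There is no effect on efficacy, power or error rates. The change should be made because the gap concerns subject safety and is cheap to close.

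**What to change.** - Add a pregnancy test to the pre-infusion list in section 5.3.1.4, for the first infusion of each additional course.
- Carry the HCG row of Table 1 into Table 2, marked at Infusion 3 (Day X) and Infusion 5 (Day Y).
- State that a negative result is required before the infusion starts, and that a positive result invokes section 6.3, item 4, and the pregnancy follow-up in section 9.1.1.4.

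The same wording would cover a second course given before Day 32. If the sponsor also wants to detect pregnancies for follow-up to delivery, a test at the End of Study visit would be a separate addition.

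The cost is one urine test per additional course for each woman of childbearing potential, at visits where urine is already taken, with 62 tests as the ceiling at the minimum sample size. Section 14.1 requires regulatory and IRB/IEC approval for a new test, so the change is best included in the next amendment.

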#### **9.1.1. Adverse Events**

For subjects who receive only 1 treatment course of GAMMAPLEX on Days 1 and 2, AEs will be documented from the date the informed consent form is signed until the End of Study visit on Day 90. For subjects who receive (an) additional course(s) of GAMMAPLEX, AEs will be documented from the date the informed consent form is signed until the End of Study visit which for this group of subjects is 90 days, approximately 3 months, after the first infusion of the last course of GAMMAPLEX. AEs will be reviewed and documented at each visit by examining the diary cards (for the first course of GAMMAPLEX up to Day 32) and by direct questioning of the subject.

The investigator will attempt to establish a diagnosis of the AE based on signs, symptoms, and/or other clinical information. It is the diagnosis that should be documented as the AE and not the individual symptoms.

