##### *Infusion-Related Adverse Events*

All AEs that occur from the start of the infusion until 72 hours after the infusion will be recorded as infusion-related, but will not necessarily be related to GAMMAPLEX per se.

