## **10.4. Safety Analyses**

### **10.4.1. Adverse Events**

The number of infusions in which an AE occurs during an infusion or within 72 hours after the infusion stops will be tabulated. A summary table including the following will be produced:

- number of subjects with AEs
- number of subjects with SAEs
- number of subjects who died
- number of subjects who withdrew because of AEs
- number of subjects with product-related AEs.

The nature, severity and frequency of all AEs will be listed.

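### Adverse events in the 72 hours after an infusion are captured less closely in courses 2 and 3 than in course 1, and it is unclear whether infusions 3–6 enter the 72-hour count

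*Protocol*

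**What the plan says.** The Protocol defines a 72-hour window around each infusion (Section 9.1.1.1): "All AEs that occur from the start of the infusion until 72 hours after the infusion will be recorded as infusion-related". Section 10.4.1 turns it into a count: "The number of infusions in which an AE occurs during an infusion or within 72 hours after the infusion stops will be tabulated". Section 9.1 lists the same measure as a number and percent of infusions. Neither section limits it to course 1. The synopsis, under its safety methodology, instead runs the 72 hours from the end of the last infusion and identifies that infusion as Day 2, which belongs to course 1.

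Collection differs by course:

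- **Course 1.** On the diary, Section 5.3.1.2 says: "Subjects will be instructed to complete a diary entry every day from Day 1 until Day 32 describing any AEs and concomitant medications". Table 1 has visits on Day 3 (±12 h), Day 5 (±1 day) and Day 9 (±2 days). Section 5.3.1.3 tells sites to take particular care on Day 5 over AEs in the 72 hours after the course.
- **Courses 2 and 3.** Each additional course is given as "1 g/kg on Day X and 1 g/kg on Day X+1" (Day Y and Y+1 for course 3). Section 5.3.1.5 then says: "Subjects will return for a follow-up visit 3 days after the end of each of the second and third treatment courses, if they receive them". Table 2 sets this at Day X+4 (Y+4) ±1 day, has no diary row, and carries no counterpart to the Day 5 instruction.

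Section 9.1.1 says that AEs are reviewed at each visit "by examining the diary cards (for the first course of GAMMAPLEX up to Day 32) and by direct questioning of the subject". For retreated subjects, collection continues to End of Study, "90 days, approximately 3 months, after the first infusion of the last course of GAMMAPLEX". Section 5.3.1.6 says of that visit: "All AEs reported by the subject or observed by the investigator will be recorded at each visit".

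**The concern.** A count of infusions with an AE within 72 hours is comparable between courses only if the 72 hours are observed equally well. In course 1 the diary and the Day 9 visit back up an early Day 5 visit. In a retreatment course from Day 32 on, neither backup exists, and the one early visit is allowed before the window closes for the second infusion of the course. An event that starts after that visit has to be remembered, and dated to within 72 hours of a particular infusion, at the next course or at End of Study.

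Safety at the study dose is a stated secondary objective. If capture is poorer for infusions 3–6, repeat courses may look better tolerated than the first for reasons of observation alone, and a rate pooled over all infusions may be too low. Visit windows and diaries are data-collection rules, so an analysis plan cannot recover events that were never recorded.

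**Working it through.** **Inputs**

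- Dose: 1 g/kg per infusion (Section 7.2.1). At 5 g per 100 mL (Section 3.1) this is 20 mL/kg.
- Rates (Table 3): 0.01, 0.02, 0.04 and 0.06 mL/kg/min for 15 minutes each, then 0.08 mL/kg/min to the end.
- Infusions 3 and 5 on Day X (Y); infusions 4 and 6 on Day X+1 (Y+1) (Section 5.3.1.4, Table 2).
- Follow-up at X+4 ±1 day, and End of Study at 90 ±7 days after the first infusion of the last course (Table 2).

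**The plan's own figure.** The course ends on X+1, and (X+1) + 3 days = X+4. The nominal day in Section 5.3.1.5 agrees with Table 2.

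**Infusion length, all rate steps tolerated**

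- Volume in the first hour: 15 × (0.01 + 0.02 + 0.04 + 0.06) = 1.95 mL/kg.
- Remainder: (20 − 1.95) / 0.08 = 225.6 min.
- Total: 60 + 225.6 = 285.6 min, or 4.76 h.

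**Hours observed.** For a visit on day v after an infusion on day d, the time since the infusion ended is 24 × (v − d) − c. Here c runs from 0 (visit at the clock time the infusion ended) to 4.76 h (visit at the clock time it started). The uncovered time is 72 minus that result, or zero if negative.

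| Infusion | Visit day | Hours since infusion ended | Uncovered of 72 h |
|---|---|---|---|
| 4 or 6 | X+3 | 43.2–48 | 24–28.8 |
| 4 or 6 | X+4 | 67.2–72 | 0–4.8 |
| 4 or 6 | X+5 | 91.2–96 | 0 |
| 3 or 5 | X+3 | 67.2–72 | 0–4.8 |
| 3 or 5 | X+4 | 91.2–96 | 0 |
| 3 or 5 | X+5 | 115.2–120 | 0 |

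**Same check on course 1.** After infusion 2 (Day 2), the earliest Day 5 visit is Day 4, also at 43.2–48 h. The earliest Day 9 visit is Day 7, at 24 × 5 = 120 h less up to 4.76 h, so 115.2–120 h. The Day 9 visit therefore always falls after the window has closed, and the diary covers the days between. The visit tolerance is the same in both settings; the backup is what differs.

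**Time to the next scheduled enquiry if no further course is given.** End of Study falls at X+83 to X+97. The gap from the follow-up visit is 83 − 5 = 78 to 97 − 3 = 94 days. From the day the window closes for infusion 4 or 6 (X+4) it is 79–93 days.

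**Possible effect on a pooled rate (assumed values, not from the Protocol).** Let m be the share of all infusions that come from courses 2–3, and q the share of their AE-positive infusions that is detected. Assume the true per-infusion rate is the same in all courses and capture in course 1 is complete. Then observed/true = 1 − m(1 − q).

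- m = 0.10, q = 0.90: 1 − 0.10 × 0.10 = 0.99.
- m = 0.50, q = 0.60: 1 − 0.50 × 0.40 = 0.80.

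Over m from 10% to 50% and q from 60% to 90%, the pooled rate would be 80–99% of the true rate.

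**The case against.** The best defence has five parts.

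- **Later enquiry exists.** AEs are taken by direct questioning at every visit, and Table 2 marks them at each infusion, follow-up and End of Study visit. This stands. A reader might infer that infusions 3–6 are under-ascertained as a fact, or that X+4 is the last time anyone asks. The Protocol supports neither. Late events face long recall but are not lost by design, and serious events have their own expedited reporting route (Section 9.1.2). The risk concerns non-serious events that are omitted or misdated.
- **The timing gap is narrow.** It is material only for infusions 4 and 6 and only at the earliest permitted day. This also stands. The absence of a diary, however, affects all of infusions 3–6 when retreatment starts from Day 32, the planned period.
- **Some retreatment has a diary.** A second course after Day 9 and before Day 32 is possible after discussion with the medical monitor and sponsor (Section 5.3.1.4). The diary and remaining course 1 visits would cover at least part of its window. This is an exception to the planned timing.
- **Pooling is not stated.** Sections 9.1 and 10.4.1 do not say that infusions 1–6 form one undivided rate, and the synopsis points to course 1 alone. Splitting a table by course is often left to the analysis plan, which is not at hand. So a reader may not conclude that the reported rate will be lowered. The disagreement over which infusions are counted nevertheless lies within the Protocol.
- **It is an open design choice.** Retreatment is optional, and Section 9.1.1 plainly limits the diary to course 1. That is fair, but the Day 5 instruction shows the Protocol itself regards the 72-hour count as needing dedicated collection.

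**Conclusion.** The point holds as a matter of unequal capture. For retreatment from Day 32 on there is no diary and one early visit. At the earliest permitted day that visit leaves 24–29 of 72 hours uncovered for infusions 4 and 6. At the nominal day it leaves 0–5 hours, and infusions 3 and 5 lose at most about 5 hours. If no further course follows, the next scheduled enquiry comes 78–94 days after the visit.

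The hours assume the full Table 3 rate schedule and a visit between the clock times at which the infusion started and ended. A slower infusion or an earlier visit would widen the gap, and a later visit would narrow it.

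It is also unclear whether infusions 3–6 enter the 72-hour count, because the synopsis and Sections 9.1 and 10.4.1 disagree. If they do and are pooled, the per-infusion rate may be understated. The 80–99% range only illustrates assumed inputs. The Protocol does not show that retreatment infusions will record fewer AEs, nor does it name this count as the main safety measure. The change is a cheap improvement, worth making because the loss cannot be repaired at analysis.

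**What to change.** - In Table 2 and Section 5.3.1.5, require the follow-up visit no earlier than 72 hours after the end of the second infusion of the course, with tolerance only on the late side. State the limit in hours: a calendar window opening on X+4 would still allow a visit at about 67 hours.
- Issue the existing diary card on Day X and Day Y and collect it at that visit. Add a diary row to Table 2 and amend Section 9.1.1 to match.
- Repeat the Day 5 instruction on 72-hour AEs for the X+4 and Y+4 visits.
- Reconcile the synopsis with Sections 9.1 and 10.4.1 on which infusions the 72-hour count covers, and show the count separately for infusions 1–2 and 3–6.

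The cost is protocol wording, a diary period of a few days per extra course on a card that already exists, and the loss of the X+3 visit option. Samples due at that visit move with it; if X+5 is kept as the latest day, they stay within the tolerance Table 2 already allows.
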